**Pregnancy**	
Class 1	The benefits of breastfeeding for metabolic control and for your infant’s health
**Postpartum**	
Class 2	Reinforcing knowledge about recurrent GDM and progression to T2DM
Class 3	The importance of daily exercise
Class 4	Understanding calories, proteins, carbohydrates, and fats
Class 5	How portion control can make a difference
Class 6	How to make healthy substitutes with food
Class 7	Choosing healthy food when eating out
Class 8	Increasing exercise (cognitive restructuring)
Class 9	Improving nutrition and exercise behaviors (social problem solving)
Class 10	Motivating yourself in a positive manner (assertiveness training)
Class 11	Understanding barriers to healthy choices (social problem solving)
Class 12	Getting back on track after relapse (assertiveness training)
Class 13	Working through conflict (conflict resolution)
Class 14	Putting it all Together

Beginning with class 2, the women will also participate in a weekly exercise session for 60 minutes that will include a 5-minute warm up, 30 minutes of aerobic exercise, a 10-minute cool down, and 15 minutes to go over the home-based exercise program handout of the week. Classes will include group walking, zumba dancing, and cardio kickboxing, which have been well received in our previous interventions [56,57]. At the end of each session 2–14, women will be asked to set a nutrition and exercise goal for the next week. Women will also receive an educational or motivational text message weekly from the time of enrollment until completion of their time in the study. If a woman is unable to attend a session, the interventionist will call them and make up class content over the phone.

### Phase II continued support

The experimental group women will then return to the site for a group session once a month for 3 months. They will receive a reminder phone call several days before each session. Women will be weighed and have a group discussion, run by the interventionist, who will answer questions and help women problem solve issues around nutrition, exercise, and breastfeeding. If a woman misses a session, the interventionist will call and ask how she is doing. Content will not be made up. The women will continue to receive monthly educational and motivational text messages to maintain contact.

### Integrity of the intervention

Integrity of the intervention will be assessed by observation of two randomly selected sessions per month. The project manager will use a checklist to score sessions based on content identified in the intervention protocol. Drift will be defined as teaching less than 80% of the protocol content. If drift occurs, the interventionist will be retrained until the protocol is followed consistently. We will use a checklist of behavioral indicators to assess the intervener’s skills in facilitating sessions, engaging the women, problem solving, providing positive feedback, and goal setting. Retraining will be provided as necessary.

### Wait-list control group

Women in the wait-list control group will receive usual care. Data on the women and infants will be collected at the same times as on the women and infants in the experimental group, and women will receive $10 each time they complete a data collection visit. Wait-list control group women will receive reminder calls one week before each visit. Transportation vouchers and childcare will be provided. During the study, they will receive a monthly card to thank them for their continued participation. When they have completed the Time 5 data collection, they will be offered the Phase I intervention (sessions 2–14) classes.

### Measurement

Table 2 shows the measures to be used, data sources, and measurement times. All instruments have been evaluated for their psychometric qualities in previous studies [56,57] and will be reevaluated in this study. Data will be collected at baseline at 22–36 weeks pregnant (Time 1), 6 weeks postpartum (Time 2), 4 months postpartum and completion of Phase I (Time 3), 7 months postpartum and completion of Phase II (Time 4), and 10 months postpartum, after 3 months on their own (Time 5). Completion of data collection takes approximately 45 minutes for each mother.

**Table 2 T2:** Summary of measures

**Variables and Their measurement**	**Respondent**	**T1**	**T2**	**T3**	**T4**	**T5**
**Aim 1: Feasibility**						
Process Evaluation Checklist	Project Manager		X	X	X	
Intervention Session Evaluation	Mothers	X	X	X	X	
Screening and Enrollment logs	Project Manager & Research Assistants	X				
Field Notes	Interventionists & Research Assistants	X	X	X	X	X
Intervention Attendance	Interventionists	X	X	X	X	
Data Collection Attendance	Research Assistants	X	X	X	X	X
Exit Interview	Mothers					X
**Aim 2: Maternal Outcomes**						
**Metabolic and Clinical Outcomes**						
3 hour Oral Glucose Tolerance Test ^1^ (FBG)	Mothers	X				
2 hour Oral Glucose Tolerance Test ^2^ (FBG)	Mothers		X			X
Insulin Level and HOMA-IR	Mothers	X	X			X
A1C and Lipid Panel	Mothers	X				X
Blood Pressure	Mothers	X	X	X	X	X
**Weight Status Outcomes**						
Height, Weight, Body Mass Index	Mothers	X	X	X	X	X
**Adiposity Outcomes**						
Waist Circumference	Mothers	*	X	X	X	X
Triceps & Subscapular Skinfolds	Mothers	X	X	X	X	X
**Health Behavior Outcomes**						
Adult Health Behavior Survey	Mothers	X	X	X	X	X
Health Promoting Lifestyle Profile II	Mothers	X	X	X	X	X
Accelerometry for 7 days	Mothers	X	X	X	X	X
**Self-Efficacy Outcomes**						
Eating Self-Efficacy Scale	Mothers	X	X	X	X	X
Exercise Self-Efficacy Scale	Mothers	X	X	X	X	X
Breastfeeding Self-Efficacy Scale	Mothers	X	X	X	X	X
**Aim: 3 Infant Feeding and Growth**						
Weeks until breastfeeding stopped ^#^	Mothers		X	X	X	X
Weeks exclusively breastfed ^#^	Mothers		X	X	X	X
Intensity of breastfeeding ^#^	Mothers		X	X	X	X
Weight-by-Length Z scores	Infants		X	X	X	X
**Demographic Data**	Mothers	X				

T1 (Baseline, at 22–36 weeks); T2 (6 weeks postpartum); T3 (4 months postpartum at completion of Phase I); T4 (7 months postpartum at completion of Phase II); T5 (10 months postpartum, after 3 months on their own); ^1^ 3 hour OGTT performed as part of GDM diagnosis includes fasting, 1, 2, and 3 hour glucose after a 100 g load; ^2^ 2 hour OGTT includes a fasting and 2 hour glucose after a 75 g glucose load; * Not done pregnant; ^#^ If a mother stops breastfeeding we will stop collecting data.

To assess acceptability of the intervention (Aim 1), the project manager will observe two randomly selected sessions per month to assess whether the sessions are being taught by the protocol. Participants will be asked to complete an evaluation at the completion of each session. At the Time 5 data collection, a trained research assistant will conduct a 15-minute exit interview with all experimental group women. To assess other aspects of feasibility, the project manager and research assistants will keep screening and enrollment logs on recruitment efforts; the number who were ineligible, with reasons for ineligibility; and the number who declined to participate with reasons why. The interventionists will keep field notes and collect data on attendance at each session, reasons for non-attendance, and number of make-up sessions provided. To assess the feasibility of the instruments, the research assistants will keep field notes and collect data on length of time it takes participants to complete each instrument, challenges encountered, and the ways they were resolved.

For maternal outcomes (Aim 2), research assistants blinded to the study group assignment will collect all data. The research assistants will use a standardized manual for collecting physiological and questionnaire data. Prior to each data collection, the research assistants are tested for inter-rater reliability on height, weight, waist circumference, triceps and subscapular skinfolds, and weight-for-length measurements.

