### Aims

The first aim of the study is to determine the feasibility of the intervention, including its acceptability, and further refine intervention materials and study procedures (recruitment, enrollment, intervention, retention, and data collection). The second aim of study is to test the effects of the intervention on maternal outcomes from baseline at 22–36 weeks pregnant (Time 1) to 6 weeks postpartum (Time 2), 4 months postpartum and completion of Phase I (Time 3), 7 months postpartum and completion of Phase II (Time 4), and 10 months postpartum, after 3 months on their own (Time 5). The primary maternal outcome is a decrease in fasting blood glucose and weight from baseline to 10 months postpartum. Secondary maternal outcomes include a decrease in glucose levels from the oral glucose tolerance test, insulin levels, homeostatic model assessment of insulin resistance (HOMA-IR), glycated hemoglobin A1C (A1C), lipid panel, blood pressure, and adiposity, as well as improvement in health behaviors, eating, exercise and breastfeeding self-efficacy from baseline to 10 months postpartum. The third aim of the study is to quantify the effects of the intervention on infant feeding and growth outcomes (weight status [weight-for-length]) and breastfeeding (weeks until stopped breastfeeding, weeks exclusively breastfed, and intensity of breastfeeding) from birth to 10 months postpartum.

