### Infant outcomes

For infant feeding and growth (Aim 3), we will measure breastfeeding duration and intensity as a modifiable risk factor for maternal and infant metabolic disease. We will define breastfeeding duration as the time since birth, in weeks, until the mother stops breastfeeding or expressing milk for her infant. We will define exclusive breastfeeding as the time, in weeks, until the mother introduces formula or complementary foods. We will define breastfeeding intensity as the percent of all milk feeds that are breast milk (# of breast milk feeds per day) / (# of breast milk + formula + other milk feeds per day) [73,74]. We will measure weight-for-length in infants, using standardized weight-for-length z scores [75]. Length will be measured twice and averaged using a portable length board and weight will be measured twice and averaged using a portable calibrated digital scale according to procedures.

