### Data analysis

#### Aim 1

To determine the acceptability of the intervention sessions and materials, the investigators will analyze the interventionists’ field notes and exit interviews with women, which will be tape-recorded with participants’ permission, transcribed, and analyzed for themes. The findings will be used to further adapt and refine the intervention*.* To assess other aspects of feasibility, recruitment yield will be described by the number contacted and the number screened required to yield one enrollment. Interventionists will keep attendance records for each class. Retention will be described at each time point. Statistics on data collection, such as duration of collection per woman, will also be computed at each time point. Rates of recruited, screened, and retained women will be presented by group and time point, along with 95% confidence intervals; the upper bounds will provide an estimate of worst case values for rates in a future study.

#### Aims 2 and 3

To analyze maternal outcomes, descriptive statistics will be calculated for each measure at each time point. All analyses will be conducted using an intention-to-treat approach. Standardized effect sizes for each measure will be calculated for each time point as the ratio of the mean difference between the intervention and wait-list control group to its standard deviation. Correlation matrices will be computed to describe the degree of correlation of each measure across the repeated measures for each group. For the assessment of trends in Aim 2, preliminary analyses will be conducted to determine whether, despite randomization, the intervention and control groups were unbalanced at baseline on any measured variable. Any such variable will be examined for statistically significant relationships with any of the outcome measures, and if any are found, the variable will be considered as a covariate for subsequent models.

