For each outcome mentioned in **Aims 2 and 3**, a separate linear mixed-effects model will be constructed. These will model data across all available post-baseline time points; contrasts will be constructed to evaluate the effects of the intervention over the post-baseline period, as compared to the wait-list control group, with covariate adjustment for baseline values. These models will include assessment for main effects for experimental group, time point, and site, as well as interactions, and will account for the within-site and within-subject correlation structure invoked via the study design. This approach will provide useful information in guiding the analysis of a future study. Least-squares means will be computed and plotted for each time point for each group to determine average trajectories for each measure.

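### Collection of breastfeeding intensity ends when a mother stops and no rule sets later values to 0%, so the plan as written drops known zeros from an Aim 3 comparison

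*Protocol article*

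**What the plan says.** All references are to the protocol article.

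- **Outcome.** Aims lists, among the third-aim outcomes, "intensity of breastfeeding) from birth to 10 months postpartum". Table 2 schedules it at Times 2 to 5.
- **Collection rule.** The row "Intensity of breastfeeding" in Table 2 carries the footnote "If a mother stops breastfeeding we will stop collecting data". The same footnote sits on the two duration rows (weeks until stopping, weeks of exclusive breastfeeding).
- **Definition.** Infant outcomes states: "We will define breastfeeding intensity as the percent of all milk feeds that are breast milk". The denominator is breast milk, formula and other milk feeds per day.
- **Stop time.** Infant outcomes counts duration in weeks from birth "until the mother stops breastfeeding or expressing milk for her infant", so the stop week is itself recorded.
- **Analysis.** Data analysis, Aims 2 and 3, says that for each outcome "a separate linear mixed-effects model will be constructed", and of these models: "These will model data across all available post-baseline time points". It also plans a standardised effect size per measure and time point, and the Power analysis section intends an effect size for each maternal and infant outcome.
- **Principle.** "All analyses will be conducted using an intention-to-treat approach".

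The article does not say that intensity is 0% after stopping. It does not say that it is missing either.

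**The concern.** After a mother has stopped, her intensity is a known value, not an unknown one: no breast milk feeds over a positive number of other milk feeds is 0%. The footnote ends collection at exactly that moment, and the analysis uses the data that are available. Unless zeros are filled in, whether a visit has an intensity value depends on the outcome itself.

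Stopping happens after randomisation, and the intervention is built to change it. Experimental women get a prenatal breastfeeding class, weekly contact about breastfeeding until classes start at 6 weeks postpartum, and access to a lactation consultant. If that support works, more experimental women stay under observation, and some of those retained may breastfeed at low intensity. The success shows up as zeros avoided, but the zeros are not in the data. A real benefit on intensity could then be reported as no effect or, in some configurations, as harm. The article says that its models are meant to guide the analysis of a future study, so such an estimate would carry forward.

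**Working it through.** **Plan's own figure.** There is none for this outcome. The article gives no continuation rate and no expected intensity, and its power statement is not specific to intensity. Every rate and intensity below is therefore an assumption.

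**Step 1. What the rule leaves in the data.** Let p be the share still breastfeeding at a time point and m the mean intensity among them.

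- Mean over all women, with zeros: p × m + (1 − p) × 0 = p × m
- Mean over visits with a collected value: m

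The difference between arms is therefore p_E × m_E − p_C × m_C over all women, but m_E − m_C in the collected data. The second expression does not contain the effect on continuation.

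**Step 2. Size at Time 5 under assumed inputs (E = experimental, C = control).**

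| p_E / p_C | m_E / m_C | All women, zeros kept | Continuers only |
|---|---|---|---|
| 50% / 30% | 70 / 70 | 35 − 21 = +14 | 0 |
| 50% / 30% | 65 / 75 | 32.5 − 22.5 = +10 | −10 |
| 55% / 40% | 60 / 70 | 33 − 28 = +5 | −10 |
| 65% / 50% | 55 / 60 | 35.75 − 30 = +5.75 | −5 |
| 40% / 40% | 70 / 70 | 28 − 28 = 0 | 0 |

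In the first two rows, with the 40 completers per arm that the Power analysis section expects, the Time 5 comparison rests on 40 × 0.50 = 20 against 40 × 0.30 = 12 women.

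**Step 3. Does a mixed model repair this?** A likelihood-based model also uses the earlier visits of women who stop later, so Step 2 does not settle it. A simulation was run with 40 women per arm, 150 runs and a random-intercept model with group, time and their interaction. Assumed shares breastfeeding at Times 2 to 5 were 80/68/58/50% (experimental) and 70/52/40/30% (control). Women with higher underlying intensity were made more likely to continue. The model had no site or cluster term, and no baseline term (intensity is not measured at Time 1).

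| Underlying mean intensity E / C | Time 5 difference, zeros kept | Mixed model, visits after stopping absent | Raw continuers |
|---|---|---|---|
| 70 / 70 | +14.5 | −2.0 | −3.2 |
| 66 / 74 | +9.9 | −9.4 | −9.9 |

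In the first scenario about 60 of 80 women and 177 of 320 visits contribute a value. Women who never breastfed or stopped before Time 2 contribute nothing. The mixed-model estimate lies close to the continuer contrast, because for women who stopped it borrows from women who went on breastfeeding.

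**The case against.** The footnote is a rule about collection, not about the analysis set. On the two duration rows, ending collection at the event is right and makes nothing missing. Staff may simply stop asking once the answer is known. Because the stop week is recorded, every later zero can be derived, and that coding could sit in a full protocol or analysis plan that is not shown. Intensity is also only one of three breastfeeding measures under the third aim, and an effect on continuation would still show in weeks until stopping.

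Much of this stands, and it limits the point. Three stronger readings are tempting but not supported:

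- **That the plan treats true zeros as missing.** No sentence says so. It follows only if the footnote and the available-data model are applied literally with nothing added.
- **That the mixed model compares continuing breastfeeders only.** It also uses earlier visits of women who stop later. The description fits the means and effect sizes at each time point, not the model.
- **That a sign reversal is to be expected.** It appears where experimental continuers are assumed to have clearly lower intensity than control continuers. The intervention also supports women while they breastfeed, so equal or higher intensity is as plausible. With equal underlying intensity the simulated benefit is mainly lost, with little reversal.

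What does not stand is that this is merely detail left to another document. The article states a rule that ends observation because of the outcome, pairs it with an available-data analysis, and promises intention to treat. Those statements do not fit together without a zero rule, and that zeros are easy to derive is a reason to state the rule.

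**Conclusion.** The point holds in a limited form. As written, visits after stopping have no intensity value. Means and effect sizes by time point are then among continuers, and the mixed model extrapolates non-zero intensity to women who stopped. This conflicts with the stated intention-to-treat approach, because stopping is a post-randomisation outcome that the intervention targets.

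Under the assumed inputs, a benefit of about 14 points at 10 months falls to roughly zero (0 among continuers, −2.0 from the mixed model). Where continuer intensity is also assumed lower in the experimental arm, a benefit of 5 to 10 points becomes a deficit of 5 to 10. If continuation and continuer intensity are equal in both arms, there is no bias. The documents do not say which case applies.

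The issue concerns intensity alone. The primary outcomes (fasting glucose and weight) and the two duration measures are not affected.

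**What to change.** - Keep the footnote for the two duration rows.
- For intensity, state that it is set to 0% at every scheduled time point after the recorded stop week, including for women who never breastfed. Take the stop week from the duration definition, which counts expressing milk as continuing.
- Include all randomised mother-infant pairs in the planned model and in the effect sizes at each time point, with those zeros. Visits missing because a woman left the study while still breastfeeding remain missing.
- Report intensity among continuers as descriptive only.
- Leave the choice of model for a bounded outcome with many zeros to the analysis plan. It should allow for the small number of clusters: two sites with four groups each gives about eight, too few for standard cluster-robust errors to be relied on.

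The cost is one sentence and one derivation step. No extra visit or question is needed: the stop week is already collected, and Table 2 schedules other measures on these mothers and infants at Times 2 to 5.

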### Metabolic and clinical outcomes

#### Oral Glucose Tolerance Test (OGTT)

The results of the mothers’ 3-hour OGTT will be copied from the medical record as Time 1 (baseline) data. The mother’s 2-hour OGTT will be scheduled through the outpatient laboratory and laboratory results will be received by secure fax from the laboratories. Women diagnosed with GDM will have two or more 100 g OGTT values exceeding established thresholds: (fasting 95, 1 h 180, 2 h 155, 3 h 140 mg/dL) [55]).

#### Insulin levels

Insulin will be measured from a fasting sample of venous blood. Aliquots of plasma will be separated, labeled and stored at −80 degrees Celsius. Insulin testing will be completed at Rex Healthcare and WakeMed laboratories. Both laboratories use the same radioimmunoassay kit, which has less than 1% cross-reactivity with C-peptide and proinsulin. The inter-assay variation for insulin is 12% and intra-assay cross-reactivity is 11%, which is well within acceptable levels. These assessments will allow us to confirm the validity of the HOMA- IR. Normal values are 5–20 micro units per milliliter while fasting [1,2].

#### HOMA-IR

The HOMA-IR estimates the steady state of beta cell functioning and insulin sensitivity [60]. HOMA-IR has been shown to discriminate across race and ethnic groups and provides a good approximation of more complex tests [60]. Fasting glucose and insulin will be drawn on all study participants by experienced laboratory personnel at either Rex Healthcare or WakeMed. The formula to be used is: (fasting insulin (IU/ml) × fasting glucose (mmol/l)/22.5 [60]. Greater HOMA-IR values indicate reduced insulin sensitivity. A value over 2.2 is indicative of insulin resistance [60].

#### Glycated hemoglobin (A1C)

A1C is measured using an immunoassay that measures the concentration of a macromolecule in a solution through the use of an immunoglobulin. A1C will be drawn on all study participants by experienced laboratory personnel at either Rex Healthcare or Wake Med. An A1C ≥ 6.5 will be considered a diagnosis of type 2 diabetes [1,2]. and those women will be excluded from the study and referred to an endocrinologist.

